**Fig. 1 Fig1:**
[figure not shown]
Trial flow chart

#### Criteria for discontinuing or modifying allocated interventions {11b}

No specific criteria for modifying allocated interventions were defined since this is a punctual intervention. However, participants in both arms presenting a non-MSKD condition after assessment will be excluded from the study and will receive usual ED physician care outside the trial according to their condition.

#### Strategies to improve adherence to interventions {11c}

This pragmatic trial will evaluate the impact of an assessment and intervention offered only within the ED either by a PT or a physician.

#### Relevant concomitant care permitted or prohibited during trial {11d}

There will be no restriction in terms of care during this trial. Participants will be asked to complete a treatment diary regarding compliance with ED treatments and any health services or interventions they sought for their initial problem during the follow-up period.

#### Provisions for post-trial care {30}

The main potential risk in this trial is a diagnostic error by PTs or physicians. Any adverse events will be documented within the current study, and we will ensure study participants receive the appropriate care if needed.

### Outcomes {12}

#### Baseline data collection

At trial inclusion, eligible participants will answer a series of questions covering socio-demographic characteristics, such as age, sex, gender, education level, household income, and living status. Clinical variables such as anthropometric data, affected body area, reason for consultation, CTAS level, duration of symptoms, type of disorder (traumatic/atraumatic), use of walking aids, and presence of any comorbidities will also be documented. Participants will also respond to the Patient Health Questionnaire (PHQ-9), a multipurpose instrument for screening and measuring depression [29, 30].

#### Primary outcome measure

The main outcome measure will be the Brief Pain Inventory–Short Form, Pain Interference Scale (BPI), and the primary endpoint at 4 weeks after discharge. The BPI is a self-administered questionnaire that includes seven items where the patient is asked to rate the impact of pain on various functional activities (pain interference scale) using a 10-point scale. The BPI is valid, reliable, and responsive to change in MSKD populations [31–34] and is suited for electronic administration [31, 35, 36].

#### Other patient-related outcomes

In order to further assess the impact of MSKD on function, participants will complete self-reported validated and reliable disability questionnaires relevant to the affected body area. Depending on the affected body area(s), participants will complete one or more of the following questionnaires: Neck Disability Index (NDI) for neck-related disorders [37], Oswestry Disability Index (ODI) for back-related disorders [38], short version of the Disability of the Arm, Shoulder and Hand (Quick DASH) for upper limb related disorders [39, 40], or Lower Extremity Functional Scale (LEFS) questionnaire for lower limb related disorders [41, 42]. To assess satisfaction with care, patients will be asked to complete a modified validated version of the 9-item visit-specific satisfaction questionnaire (VSQ-9) at initial discharge [43–46]. Participants will be informed that these answers will remain confidential and will not be communicated to the ED providers.

#### Health care resource utilization outcomes

The ED physician or PT will complete a standardized form following their assessment and interventions, indicating diagnoses, requests for additional medical imaging or laboratory tests (if relevant), treatment plan (e.g., conservative treatment options, medication or physiotherapy care), discharge plan, and referral to other professional or medical specialists, if relevant. Providers in both arms will have access to the patient’s full medical record. Proportion of medical imaging tests or other laboratory tests, drug prescriptions/recommendations for analgesics and for opioids, and referral to other providers after initial assessment will be recorded with this form and confirmed with the participants’ medical file. Any adverse events, re-visits to the ED for the same complaint, and any incidents associated with care will be questioned at each time point during follow-up and completed by consulting patients’ medical files.

#### Health care costs

The EQ-5D-5L will be the primary outcome measure for the cost analysis outcomes. It is a generic health-related quality of life questionnaire for which validity has been established. It has been widely used in economic evaluations, including in trials with patients suffering from MSKD and in our pilot RCT [44]. Time-driven activity-based costing (TDABC) will be used to measure the costs of all resources (personnel, consumables, overhead, etc.) utilized during the ED visit and any episode of care during follow-up. TDABC combines process mapping and resource-level costing and has been used to measure health care costs around the world [47–54]. The overarching objective of this methodology is to calculate the costs of all resources (personnel including PT and physician salaries, consumables, overhead, etc.) consumed as a patient moves along a care pathway, which is determined via a collaboration between clinical and administrative staff and each step of the pathway represents direct and indirect resources consumed when providing patient care. The care pathway in this case includes the ED visit and any episode of care during follow-up visits. The TDABC methodology will be applied at the six different sites and hence allowing us to map and compare the care pathway used in all the different sites and potentially compare them to outcomes achieved using the EQ-5D-5L.

#### Wait to initial assessment and ED length of stay measures

Wait in the ED, which is defined as the time between the arrival in the ED and the initial evaluation by a physician or a PT will be recorded. The total length of stay in the ED will also be recorded in minutes by research professionals onsite.

#### Follow-up measures

The questionnaires will be sent by email using the Research Electronic Data Capture (REDCap™) platform or completed over the phone, depending on patient preference. All included questionnaires have been validated for use electronically or over the phone. REDCap is a secure web platform. In order to limit loss to follow-up, we will validate with participants at each time point their contact information and preferred means of communication. Participants will also be asked to complete a treatment diary regarding compliance with ED treatments and any health services or interventions they sought for their initial ED visit during the follow-up period (Fig. 1, Table 1)

**Table 1 Tab1:** Time schedule of enrollment, interventions, and assessments

	Study period					
	Enrolment	Allocation	Post-allocation			Close out
**Time point**	***−t***_**1**_	**0**	***t***_**1*****(post-eval)***_	***t***_**2*****(4 weeks)***_	***t***_**3*****(12 weeks)***_	***t***_**4*****(26 weeks)***_
**Enrollment**						
**Eligibility screen**	**X**					
**Informed consent**	**X**					
**Sociodemographic data**	**X**					
**Allocation**		**Stepped-wedge design: randomization according to time periods across all sites (3 steps of 6 weeks periods—2 sites switching to experimental arm at each step)**				
**Interventions**						
**Usual ED physician care**						
**PT-led APP care**						
**Assessments**						
**BPI**	**X**			**X**	**X**	**X**
**Disability questionnaires (NDI, ODI, LEFS, quickDASH)**	**X**			**X**	**X**	**X**
**EQ-5D-5L**	**X**			**X**	**X**	**X**
**PHQ-9**	**X**					
**Numerical Pain Scale**			**X**			
**Standardized evaluation form (PT/MD)**			**X**			
**VSQ-9**			**X**			
**Health care resources utilization and health care costs:** **Treatment diary** **Patients’ medical file**				**X**	**X**	**X**

*ED* emergency department, *APP* advanced practice physiotherapy, *BPI* Brief Pain Inventory, *NDI* Neck Disability Index, *ODI* Oswestry Disability Index, *LEFS* Lower Extremity Functional Scale, *DASH* Disabilities of the Arm, Shoulder and Hand, *PHQ-9* Patient Health Questionnaire-9, *VSQ-9* Visit-Specific Questionnaire-9

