**Methods:**

This trial is a multicenter stepped-wedge cluster randomized controlled trial (RCT) with a cost analysis. Six Canadian EDs (clusters) will be randomized to a treatment sequence where patients will either be managed by an ED APPT or receive usual ED physician care. Seven hundred forty-four adults with a minor MSKD will be recruited. The main outcome measure will be the Brief Pain Inventory Questionnaire. Secondary measures will include validated self-reported disability questionnaires, the EQ-5D-5L, and other health care utilization outcomes such as prescription of imaging tests and medication. Adverse events and re-visits to the ED for the same complaint will also be monitored. Health care costs will be measured from the perspective of the public health care system using time-driven activity-based costing. Outcomes will be collected at inclusion, at ED discharge, and at 4, 12, and 26 weeks following the initial ED visit. Per-protocol and intention-to-treat analyses will be performed using linear mixed models with a random effect for cluster and fixed effect for time.

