### Objectives {7}

Thus, the aim of our project is to evaluate the impact of an APP-led model of care compared to usual physician ED care for persons presenting with minor MSKD. The specific objectives are:To compare the effectiveness of both types of care in terms of patient-related outcomes for patients with minor MSKD in six Canadian EDs, at discharge from the ED and 4, 12, and 26 weeks after the ED consultation, on the following outcomes:Primary outcome: the Brief Pain Inventory (BPI) – Interference of pain on function subscaleSecondary outcomes: pain intensity, disability, patient satisfaction with care, and adverse events.To compare health care resource utilization between both types of care at ED discharge and at 4, 12, and 26 weeks after the initial consultation, including proportion of ED return visits for the same complaint, medication prescriptions, prescriptions for imaging and laboratory tests, and referral to other health care providersTo compare both types of care in terms of health care costs from the public payer’s perspective and perform a cost-utility analysis, at ED discharge and at 4, 12, and 26 weeks after the initial consultationTo compare wait to initial assessment and ED length of stay between both types of care for the evaluation and treatment of participants during their ED visit

We hypothesize that integrating APP-led care in the ED will be at least as effective as usual ED physician care for patients with a MSKD, in terms of patient-related and health care resource utilization-related outcomes. Furthermore, health care costs will be lower in the APP-led care arm.

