### Data collection and management

#### Plans for assessment and collection of outcomes {18a}

All data will be collected using the REDCap platform. Outcome measures will be collected at inclusion, before ED discharge, and at 4-week, 12-week, and 26-week follow points (Table 1).

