## Discussion

Current evidence shows that an increasing number of MSKD patients turn to EDs for care [57]. Many studies have shown that the current management of MSKD is often not optimal and is associated with poor outcomes [2, 15, 58]. Current training of ED physicians covers the management of serious, complex, and potentially life-threatening disorders. Training for other non-life-threatening disorders such as MSKD is often more limited. Also, current medical management of MSKD is often associated with high rates of opioid prescriptions [58, 59]. Indeed, Canada is struggling with an opioid crisis and many patients presenting to the ED for painful MSKD are discharged with an opioid prescription [60]. Even though opioids should not be the first-line treatment for the management of MSKD [58, 61–63], they represent a significant part of the current medical management of MSKD pain in the ED. Conversely, recommended non-pharmacological approaches [64], such as physiotherapy, are scarcely used. Studies involving PTs as primary care providers for patients presenting with MSKD have shown that early access to care leads to better outcomes as PTs are able to take more time with patients and can provide more complete education to patients and offer self-management strategies [65, 66]. Patients’ satisfaction with MSKD care is often significantly higher with PT led-care compared to physician care [66]. Our team recently completed two studies that serve as a foundation to the current trial. We first assessed the diagnostic concordance as well as management of ED patients with MSKD by ED PTs in comparison with usual ED physician care in two EDs [43]. The results showed that there was a high diagnostic agreement between PTs and ED physicians with no serious or non-MSKD pathologies being missed by PTs and no adverse event recorded. ED PTs were shown to recommend more physiotherapy care for MSKD, in comparison with usual ED medical care. ED physicians prescribed significantly more prescription drugs, including opioids, to manage MSKD in comparison with ED PTs. [43] The second study by our team was a single-blind pilot feasibility RCT conducted in another ED [44]. Although based on per-protocol analysis, patients that received ED PT-led care had significantly lower pain interference and pain intensity levels at 1 and 3 months after the initial ED visit. Lower proportions of prescription medication, including opioids and lower rates of re-visits to the ED, were also observed in comparison with patients receiving usual medical care at 1 month. ED PT-led care was also associated with significantly fewer prescriptions of medical imaging tests [44].

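### Pain intensity is promised at ED discharge and at 4, 12 and 26 weeks, but Table 1 schedules its only stated measure once, after the ED assessment, with no enrolment value

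*Protocol article*

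**What the plan says.** Objectives {7} sets one list of times for the patient-related outcomes of the first objective: "at discharge from the ED and 4, 12, and 26 weeks after the ED consultation, on the following outcomes". Pain intensity comes first among the secondary outcomes under that list, followed by disability, satisfaction and adverse events.

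The abstract gives the same times without exception by instrument: "Outcomes will be collected at inclusion, at ED discharge, and at 4, 12, and 26 weeks following the initial ED visit". Plans for assessment and collection of outcomes {18a} repeats them and refers to Table 1, and Participant timeline {13} also points there.

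In Table 1 the "Numerical Pain Scale" is marked only at t1 (post-evaluation). The BPI, the disability questionnaires and the EQ-5D-5L are marked at enrolment and at 4, 12 and 26 weeks, but not at t1.

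On the content of the BPI, the Primary outcome measure section says: "The BPI is a self-administered questionnaire that includes seven items". It goes on to describe those items as ratings of how far pain affects functional activities. No pain-severity item is mentioned, and Outcomes {12} describes no pain-intensity measure at all.

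**The concern.** A named secondary outcome has promised comparison times for which the schedule collects no stated data. If the sites follow Table 1, pain intensity at 4, 12 and 26 weeks cannot be compared, and values not collected cannot be recovered at analysis.

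The single value that is collected comes after the patient has been seen by the physiotherapist or physician, with no earlier value on the same scale. That matters in this design. Sites know their sequence from the start (Concealment mechanism {16b}), patients are approached and consented one by one (Recruitment {15}), and neither patients nor providers are blinded (Who will be blinded {17a}). The patients who enter may therefore differ between control and intervention periods. A post-assessment pain score alone cannot separate a difference in starting pain from an effect of the model of care.

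**Working it through.** The check needs no formula beyond a count. It sets the promised times against the marks in Table 1.

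**Step 1. Is the table read correctly?** The columns are enrolment, allocation (0), t1 (post-evaluation), t2 (4 weeks), t3 (12 weeks) and t4 (26 weeks). Two rows can be checked against the text. The VSQ-9 is marked in the same column as the pain scale, and Other patient-related outcomes places the VSQ-9 at initial discharge. The BPI is marked at 4 weeks, where the Primary outcome measure section puts the primary endpoint. The columns are aligned, so the single pain-scale mark is not an artefact of text extraction.

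**Step 2. Marks in Table 1.** The allocation column has no assessment marks and is left out. The last column counts marks among discharge, 4, 12 and 26 weeks.

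| Measure | Enrolment | t1 | 4 wk | 12 wk | 26 wk | Of the four times |
|---|---|---|---|---|---|---|
| Numerical Pain Scale | – | X | – | – | – | 1 of 4 |
| BPI | X | – | X | X | X | 3 of 4 |
| Disability questionnaires | X | – | X | X | X | 3 of 4 |
| EQ-5D-5L | X | – | X | X | X | 3 of 4 |
| VSQ-9 | – | X | – | – | – | 1 of 4 (text asks for discharge only) |

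**Step 3. Pain intensity.** Promised times: 4. Times with a scheduled pain-scale mark: 1. Without a source: 4 − 1 = 3, and 3/4 = 75%. The one covered time has no enrolment mark.

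**Step 4. Can another row supply it?** Only the BPI could. As described, it consists of seven interference items, and Objectives {7} likewise names only the interference subscale. Taking the text at its word, the BPI row gives no pain intensity, and the count in step 3 stands.

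**Step 5. The primary endpoint.** BPI interference has an enrolment mark and a 4-week mark, so the primary comparison and the sample size calculation do not depend on this point.

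**The case against.** The strongest reply is that the BPI row may carry more than interference. The article speaks of a subscale, of the short form (Primary outcome measure; Sample size {14}) and, in the abstract, of the questionnaire as a whole. The marks are also exactly complementary: the BPI at enrolment and the three follow-ups, the pain scale only at t1. That pattern would fit a single pain item filling the one contact where the BPI is not given. This reading is possible and lowers confidence. But no section states it, and the only description of the items goes against it. Even if it is right, the protocol must say which items measure pain intensity, and the discharge value would still be on an instrument with no enrolment value.

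Three stronger readings are tempting, and the article does not support them.

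- A reader might infer that the discharge comparisons of BPI, disability and cost-utility are lost. The time list is pooled wording: satisfaction stands under it too, yet is collected only at discharge. The third objective joins costs, which are meaningful at discharge, with cost-utility under one list and does not name the EQ-5D-5L. The link comes from Health care costs, "The EQ-5D-5L will be the primary outcome measure for the cost analysis outcomes", and from the abstract's general collection statement. Correcting the wording changes no result.
- A reader might infer that no baseline adjustment is possible for the discharge pain score. The BPI, disability questionnaires, EQ-5D-5L and PHQ-9 are all taken at enrolment, and Statistical methods {20a} allows adjustment where baseline differences are seen. What is missing is an enrolment value on the same scale.
- A reader might infer that the trial fails to confirm its pilot, whose physiotherapist-led patients "had significantly lower pain interference and pain intensity levels at 1 and 3 months after the initial ED visit". That is background in the Discussion; confirming it is not an objective.

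**Conclusion.** The point holds for pain intensity. The first objective and Table 1 contradict each other: three of the four promised comparisons (75%) have no stated data source, and the remaining one, at discharge, lacks a same-scale enrolment value. This rests on two assumptions: that Table 1 is the operative schedule, as {13} and {18a} indicate, and that its BPI row means the interference scale described in the text. The first is well supported. The second is what the article says but could be overturned by the full questionnaire, so confidence is moderate.

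The matter should be corrected, but it concerns a secondary outcome. The mismatch at discharge for the BPI, disability questionnaires and EQ-5D-5L is a minor matter of wording.

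**What to change.** 1. Add the Numerical Pain Scale to Table 1 at enrolment, 4, 12 and 26 weeks, describe it in Outcomes {12} as the pain-intensity measure, and adjust its analysis for the enrolment value.
2. If BPI severity items are in fact administered at enrolment and follow-up, name them as the pain-intensity measure for those times. Still add the Numerical Pain Scale at enrolment, so that the discharge value has a baseline on its own scale.
3. As an alignment of wording only, rephrase the first and third objectives, and the general statements in the abstract and {18a}, so that they do not imply that the BPI, disability questionnaires or EQ-5D-5L are measured at discharge. Discharge remains for pain intensity, satisfaction, ED resource use and ED costs.

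The cost is one questionnaire item at four contacts already scheduled (one contact under item 2), a change to the REDCap forms, and a protocol amendment, which the article says needs approval by all the committees. Visits, sample size, allocation and care are unchanged.

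The change is best made before the first patient is enrolled. All sites start in the control condition, so an item added after recruitment begins would lack enrolment values mainly for control patients.

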### Participant timeline {13}

The participant timeline is presented in Table 1.

### Sample size {14}

The main hypothesis is that APP-led care will be at least as effective as usual ED physician care based on the results of our literature review [16] and ED studies [43, 44]. The sample size required is based on a target effect size of 0.35, using the primary outcome measure, the BPI short form, with a two-sided significance level of 0.05 and a power of 0.80. An intra-cluster correlation coefficient of 0.004 was assumed based on a prior cluster RCT that also used the BPI short form as a primary outcome [55]. The calculation further assumed 6 clusters with an exchangeable correlation structure within clusters, a total of 3 sequences (steps), and two clusters changing treatment per sequence. With these assumptions, the trial will be adequately powered if 27 individuals are accrued per cluster per sequence. Hence, we will recruit 31 patients per site per sequence, accounting for a potential loss to follow-up of 15%. The total sample of 744 participants (124 per site) will provide an adequate sample size to meet our objectives.

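### The main hypothesis is a no-worse-than claim, but the 80% power is for detecting a two-sided difference of 0.35, and no margin is stated

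*Protocol article*

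**What the plan says.** Under Objectives {7} the article writes "We hypothesize that integrating APP-led care in the ED will be at least as effective as usual ED physician care", for patient-related and resource-use outcomes. Sample size {14} makes this the principal claim: "The main hypothesis is that APP-led care will be at least as effective as usual ED physician care".

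The next sentence of Sample size {14} sets the calculation on a "target effect size of 0.35, using the primary outcome measure, the BPI short form". The same sentence then fixes the error rates: "with a two-sided significance level of 0.05 and a power of 0.80". The remaining inputs are an intra-cluster correlation of 0.004, six clusters with exchangeable correlation, three sequences of two clusters, and 27 evaluable patients per cluster per period, raised to 31 for loss to follow-up (744 in total).

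The primary endpoint is BPI pain interference at 4 weeks. Statistical methods {20a} plans a linear mixed model with a fixed effect for intervention status, and both intention-to-treat and per-protocol analyses. The article gives no margin and does not describe 0.35 as one.

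**The concern.** A claim that one model of care is no worse than another is tested by asking whether a confidence limit excludes a deficit larger than some agreed size. A two-sided test of no difference asks something else. If that test is not significant, it has not shown the two models to be alike; it has only failed to separate them.

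The mismatch matters most when the hypothesis is true in its simplest form. If the two models have equal effect, a two-sided 5% test is non-significant about 95% of the time and favours physiotherapist-led care 2.5% of the time. That holds for any such test. Here, though, equality is a case in which the main hypothesis is correct, and the article gives no route from the expected result to that conclusion. The team would have to draw no conclusion, treat non-significance as support, or choose a margin after seeing the data. The stated 80% power does not describe the chance of confirming the stated hypothesis unless 0.35 is also the margin.

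**Working it through.** **Inputs.** From Sample size {14}: 6 clusters, 3 sequences of 2, exchangeable correlation, ICC 0.004, target 0.35, two-sided 0.05, power 0.80, 27 evaluable per cluster-period. From Trial design {8}: 4 periods. Assumption: 0.35 is in units of the total SD (set to 1), since no SD is given. Step 1 supports this reading.

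**Step 1. Reproduce the plan's figure.** The Hussey-Hughes variance for a cross-sectional stepped wedge with I clusters and T periods is

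Var = I·s²·(s² + T·τ²) / [(I·U − W)·s² + (U² + I·T·U − T·W − I·V)·τ²]

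- The treatment patterns are 0111, 0011 and 0001, two clusters each.
- U (treated cluster-periods) = 2 × (3 + 2 + 1) = 12.
- W (squared column totals) = 0² + 2² + 4² + 6² = 56.
- V (squared row totals) = 2 × (9 + 4 + 1) = 28.
- τ² = 0.004 and s² = 0.996/27 = 0.03689.
- Numerator = 6 × 0.03689 × (0.03689 + 0.016) = 0.011706.
- Denominator = (72 − 56) × 0.03689 + (144 + 288 − 224 − 168) × 0.004 = 0.5902 + 0.1600 = 0.7502.
- Var = 0.015604, so SE = 0.1249 SD.

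Power for a difference of 0.35 = Φ(0.35/0.1249 − 1.96) = Φ(0.842) = 80.0%. With 26 per cluster-period it is 78.7%, so 27 is the smallest number that reaches 80%. A one-sided 0.05 test would need only 21. The plan's 27 is therefore the answer for a two-sided test of a 0.35 SD difference. The recruited total also checks: 31 × 4 × 6 = 744.

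**Step 2. What a null-looking result would show.** The 95% interval half-width is 1.96 × 0.1249 = 0.245 SD. An estimate of exactly zero would still be compatible with physiotherapist-led care being worse by about 0.245 SD. Whether that is tolerable cannot be judged without a margin.

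**Step 3. Power for the hypothesis as worded.** With a true difference of zero and one-sided 0.025 (the upper limit of a two-sided 95% interval), non-inferiority power at margin M is Φ(M/0.1249 − 1.96). The margins below 0.35 are assumptions, used only to show the range.

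| Margin (SD) | Power at 27 per cluster-period | Evaluable per cluster-period for 80% (total over 24) |
|---|---|---|
| 0.35 | 80% | 27 (648) |
| 0.30 | 67% | 38 (912) |
| 0.25 | 52% | 58 (1,392) |
| 0.20 | 36% | 95 (2,280) |

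**The case against.** The case on the other side is that this is a difference trial with a loosely worded hypothesis. The article never uses the terms non-inferiority, equivalence or margin. Its aim is to compare effectiveness, its test is two-sided, and its figure is a target effect. The Discussion reports a pilot trial in which physiotherapist-led care gave significantly lower pain interference at 1 and 3 months, so sizing for a benefit is natural. On this view one reworded sentence settles the matter. Further, the article condenses a longer protocol, and decision rules are often left to the analysis plan.

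Part of this stands. The absence of a confidence-limit rule from Statistical methods {20a} carries no weight by itself, and rewording is an adequate remedy. But the no-worse-than claim appears twice and is labelled the main hypothesis. Objectives {7} also sets it beside a plainly directional claim, that costs will be lower. The hypothesis and the calculation sit next to each other in Sample size {14} and do not match, which is a conflict between stated elements and not an omission.

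A reader might go further and infer three things that the documents do not support:

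- **That the trial cannot establish its hypothesis.** It can: a significant benefit shows that physiotherapist-led care is at least no worse.
- **That the sample size is wrong.** It reproduces exactly, and the same number gives 80% power for non-inferiority if 0.35 SD is justified as the margin.
- **That the team intends to read non-significance as support.** Nothing in the article says so. The gap is that nothing rules it out.

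**Conclusion.** The point holds as a mismatch between the main hypothesis and the test for which the trial is sized. The 80% power is for detecting a 0.35 SD difference. It carries over to the stated hypothesis only if 0.35 SD is also the accepted margin, which the article does not say; at the assumed tighter margins in the table, power falls to between 67% and 36%. What is missing is a valid conclusion for a similar or non-significant result, in a trial whose main claim could be true in just that case.

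The figures rest on 0.35 being in SD units, a true difference of zero, 27 evaluable patients per cluster-period and a large-sample normal approximation. A small-sample correction for six clusters would lower every power shown and widen the interval, but would leave the mismatch as it is.

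**What to change.** Make one of two changes before outcome data are compared by arm. Interim analyses {21b} plans a look at the 1-month follow-up, which is about when the primary endpoint falls, so the change should precede it.

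**(a) Keep the hypothesis and give it a rule.**
- State a clinically justified margin on the 4-week BPI interference score, with the SD used to relate it to SD units. The 0.35 target should not become the margin by default: a benefit worth detecting is not the same as a deficit that can be tolerated.
- Conclude that physiotherapist-led care is no worse only if the upper limit of the two-sided 95% interval (physiotherapist-led minus usual care, higher scores meaning more interference) lies below the margin in both the intention-to-treat and the per-protocol analysis.
- If that is met, test superiority on the same interval, which needs no further alpha.
- Restate the power for the chosen margin.

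**(b) Reword the main hypothesis as superiority** with a target difference of 0.35 SD, in both Objectives {7} and Sample size {14}, and state that a non-significant result will not be taken as evidence that the models are equally effective.

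Either way the cost is wording and agreement, with the planned number unchanged. Under (a), the stated power becomes less favourable if the justified margin is below 0.35 SD, and holding 80% would take the larger totals in the table. Under (b), the trial gives up the broader claim.

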### Trial design {8}

This project is a multicenter pragmatic stepped-wedge (3 steps with 4 periods of 6 weeks each) cluster RCT with a cost analysis conducted in six Canadian EDs.

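### Recruiting 31 per site per period does not cover 15% loss (26.35 remain, 27 are needed), and the unit “per sequence” does not give 124 per site or 744

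*Protocol article*

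**What the plan says.** The Sample size section of the protocol article sets the calculation up "with a two-sided significance level of 0.05 and a power of 0.80", "based on a target effect size of 0.35, using the primary outcome measure, the BPI short form". It adds that "An intra-cluster correlation coefficient of 0.004 was assumed" and specifies "6 clusters with an exchangeable correlation structure within clusters, a total of 3 sequences (steps), and two clusters changing treatment per sequence". It concludes that "the trial will be adequately powered if 27 individuals are accrued per cluster per sequence", and goes on: "Hence, we will recruit 31 patients per site per sequence, accounting for a potential loss to follow-up of 15" (per cent). The totals given are 124 per site and 744 overall.

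The Trial design section describes the layout as "3 steps with 4 periods of 6 weeks each". The section on sequence generation confirms that the first of these is a baseline period in which every site delivers usual care.

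**The concern.** Two things in the same short section do not fit together.

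- **Loss allowance.** The step from 27 to 31 is presented as covering 15% loss to follow-up, but 85% of 31 is less than 27. If 27 is the smallest cell that gives 80% power, the trial as sized does not deliver that power at the loss it plans for.
- **Unit.** The section defines three sequences and recruits 31 per site per sequence, but its totals need four recruitment blocks per site. In a stepped-wedge trial a site belongs to one sequence only, so the recruitment cell is the site-period. Read literally, the sentence gives a smaller per-site target than the one stated next to it.

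**Working it through.** **Inputs.** From Sample size: standardised effect 0.35 (so total SD = 1), two-sided alpha 0.05, power 0.80, intra-cluster correlation 0.004, exchangeable structure, 6 clusters, 3 sequences of 2 clusters, 27 needed per cell, 31 recruited per cell, 15% loss, 124 per site, 744 in total. From Trial design and sequence generation: 4 periods, the first all-control.

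**Step 1: reproduce the 27.** The article does not name its variance formula. I used the Hussey–Hughes variance (cross-sectional, fixed period effects, normal approximation):

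Var = I·s²·(s² + T·t²) / [(I·U − W)·s² + (U² + I·T·U − T·W − I·V)·t²]

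- I = 6, T = 4, t² = 0.004, s² = 0.996/m, where m is the number per site per period.
- From the layout: U = 12 (treated cells), W = 0² + 2² + 4² + 6² = 56 (squared column sums), V = 2·(3² + 2² + 1²) = 28 (squared row sums).
- I·U − W = 72 − 56 = 16.
- U² + I·T·U − T·W − I·V = 144 + 288 − 224 − 168 = 40.

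With m = 27:

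- s² = 0.996/27 = 0.036889
- Numerator = 6 × 0.036889 × (0.036889 + 0.016) = 0.011706
- Denominator = 16 × 0.036889 + 40 × 0.004 = 0.750222
- Var = 0.015603, SE = 0.12491
- Power = Φ(0.35/0.12491 − 1.960) = Φ(0.842) = 80.0%

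With m = 26 the power is 78.6%. So 27 is the smallest whole number that reaches 80%. With four periods, the cell it refers to is one site in one period. If the baseline period is dropped and three periods are used, 27 gives 79.6% and misses 80%.

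**Step 2: the loss allowance.**

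- Recruit n/(1 − d) = 27/0.85 = 31.76, so 32.
- The stated 31 agrees with n·(1 + d) = 27 × 1.15 = 31.05 rounded to the nearest whole number. The article does not show its formula, so this is the likely origin, not a documented one.
- Retained from 31 at 15% loss: 31 × 0.85 = 26.35 per cell.
- Whole trial: 744 × 0.85 = 632.4, against 27 × 24 cells = 648. The shortfall is about 16.
- Largest loss that 31 can absorb: (31 − 27)/31 = 4/31 = 12.9%.

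**Step 3: the effect on power.** With m = 26.35:

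- s² = 0.996/26.35 = 0.037799
- Var = 0.012201/0.764782 = 0.015954, SE = 0.12631
- Power = Φ(0.35/0.12631 − 1.960) = Φ(0.811) = 79.1%

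| Recruited per site per period | Left after 15% loss | Power | Per site | Total |
|---|---|---|---|---|
| 31 | 26.35 | 79.1% | 124 | 744 |
| 32 | 27.20 | 80.3% | 128 | 768 |

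**Step 4: the unit.**

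- Per sequence, as written: 31 × 3 = 93 per site; 93 × 6 = 558.
- Per period: 31 × 4 = 124 per site; 124 × 6 = 744.

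Only the second reading gives the stated totals.

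**The case against.** The best reply is that very little turns on this.

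- **Size.** Power falls by 0.9 points, and the effect detectable with 80% power moves from 0.350 to 0.354. The assumed intra-cluster correlation matters more: at 27 per cell, 0.006 in place of 0.004 gives 78.5%, and 0.002 gives 81.9%. This stands, and it limits the weight of the point.
- **Timing of the loss.** The article does not say when the 15% applies. The primary endpoint is at 4 weeks and follow-up runs to 26, so loss at 4 weeks may be lower. Multiple imputation is planned, and the BPI is also collected at baseline, 12 and 26 weeks, so a missing 4-week score need not carry zero information. This makes 632 a cautious count. It does not rescue the sentence, which claims to cover 15% and covers 12.9%.
- **Method.** The 80.0% and 79.1% rest on a normal approximation that the article does not state. That is correct. It is the variant that reproduces the 27. The inflation error itself does not depend on it, since 26.35 is below 27 under any method.
- **Unit.** The totals of 124 and 744, the four periods and the described baseline period make the intention recoverable. A site with a stated target of 124 is unlikely to stop at 93. This also stands: the totals fit the four-period design, and the error is in the label.

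**Conclusion.** The point holds: the section is wrong as written on both counts. At 15% loss, 31 per site per period leaves 26.35 evaluable patients where 27 are required, about 16 short over the trial. Power is then 79.1% instead of 80%. This assumes the Hussey–Hughes variance with a normal approximation, the article's own inputs, and that patients lost contribute nothing to the 4-week analysis. The unit should be the period, because 124 and 744 cannot be obtained from three sequences.

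The consequence for the trial is small, and neither the design nor the analysis is threatened. It should still be corrected, because the published sample size claims a margin for loss that it does not have and cannot be rebuilt from its own definitions.

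**What to change.** Replace “per sequence” by “per period” in both sentences of the Sample size section, so that the cell is one site in one 6-week period. Then choose one of two statements:

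1. **Keep the size.** 31 per site per period, 124 per site and 744 in total, tolerates 12.9% loss; at 15% loss 26.35 per cell remain and power is about 79%. This costs nothing beyond a slightly less favourable power statement.
2. **Keep the 15% and the 80%.** Recruit 32 per site per period: 32 × 4 = 128 per site and 128 × 6 = 768 in total. This adds 24 patients (3.2%) and gives 80.3% power after 15% loss. The total in the abstract would change too.

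In either case, stating the follow-up point to which the 15% refers would remove the remaining ambiguity.
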